## Abstract

**Introduction:**

Patients with advanced cirrhosis have enteric bacterial dysbiosis and translocation of bacteria and their products across the gut epithelial barrier. This culminates in systemic inflammation and endotoxaemia, inducing innate immune dysfunction which predisposes to infection, and development of complications such as bleeding, sepsis and hepatic encephalopathy. This feasibility study aims to assess the safety of administering faecal microbiota transplantion to patients with cirrhosis and explore the effect of the intervention on their prognosis by achieving restoration of a healthy gut microbiome.

**Methods and analysis:**

A PROspective, randomised placebo controlled feasibility trial of Faecal mIcrobiota Transplantation is a single-centre, randomised, single-blinded, placebo-controlled study evaluating faecal microbiota transplantation (FMT) against placebo. Patients with advanced but stable cirrhosis with a Model for End-Stage Liver Disease score between 10 and 16 will be recruited. Twenty-four patients will be randomised to FMT plus standard of care (as per our institutional practice) and eight patients to placebo in a ratio of 3:1. Patients will be evaluated at baseline before the study intervention is administered and at 7, 30 and 90 days post-intervention to assess safety and adverse events. FMT/placebo will be administered into the jejunum within 7 days of baseline. The primary outcome measure will be safety and feasibility as assessed by recruitment rates, tolerability and safety of FMT treatment. Results will be disseminated via peer-reviewed journals and international conferences. The recruitment of the first patient occurred on 23 May 2018.

**Ethics and dissemination:**

Research Ethics approval was given by the London South East Research Ethics committee (ref 17/LO/2081).

**Trial registration number:**

NCT02862249 and EudraCT 2017-003629-13.

Strengths and limitations of this studyThis study is powered to assess feasibility and safety of administering faecal microbiota transplantation (FMT) to patients with cirrhosis, however, it is not statistically powered to assess for clinically relevant outcomes.This is the first study examining the effect of FMT delivered directly into the small bowel in patients with advanced cirrhosis. This trial does not involve antibiotic pretreatment in the FMT group, as has been undertaken in the USA in patients with hepatic encephalopathy.A PROspective, randomised placebo controlled feasibility trial of Faecal mIcrobiota Transplantation will assess instillation of FMT/placebo directly into the small bowel, as opposed to the colon, directly targeting small bowel bacterial overgrowth that is observed in cirrhosis.A limitation of the study is its single-blinded design, which was necessary as the FMT and placebo (saline with glycerol) are not matched.

## Introduction

Patients with advanced cirrhosis have enteric dysbiosis with small bowel bacterial overgrowth and translocation of bacteria and their products across the gut epithelial barrier.^1^ This culminates in systemic inflammation and endotoxaemia, inducing innate immune dysfunction which predisposes to infection,^2^ and development of complications such as bleeding, sepsis and hepatic encephalopathy (HE).^3^ It also plays a key role in the natural history of cirrhosis by influencing the rate of progression to advanced liver disease and terminal liver failure.^4^

Using quantitative metagenomics, our group has found 75 245 genes differentially expressed between patients with cirrhosis and healthy individuals. Over 50% of these bacterial species are of buccal origin suggesting an invasion of the gut from the mouth in cirrhosis.^5^ Patients with cirrhosis also have salivary dysbiosis associated with impaired salivary defences and systemic inflammation. Salivary dysbiosis has been shown to be greater in patients with cirrhosis who developed complications necessitating hospitalisation within 90 days. Modulating the gut microbiota in patients with cirrhosis with the non-absorbable antibiotic rifaximin has been associated with improved cognitive performance and reduction in endotoxaemia in patients with cirrhosis.^6 7^ Moreover, we have recently performed a multicentre retrospective study including 170 patients in which rifaximin-α therapy given for 90 days significantly (1) reduced hospital readmission rates after 3 months treatment, impacting significantly on the National Health Service resource burden and (2) reduced overall liver disease severity (as measured by the Child Pugh and Model for End-Stage Liver Disease (MELD) scores) raising the possibility that modulation of gut microbiota may significantly modify the natural history of chronic liver failure.^8^

These data constitute in our view ‘proof of principle’ that modifying the gut microbiota in patients with cirrhosis improves clinical outcomes. Rifaximin-α was approved by National Institute for Health and Care Excellence (NICE) for the prevention of the recurrence of overt HE in cirrhosis^9^ but considerable concern remains regarding whether long-term antibiotic prescription will result in a change in bacterial function and virulence rather than a simple reduction in bacterial population and whether this may drive bacterial resistance to antibiotics in an already functionally immunocompromised population. The question was, therefore, raised as to whether directly, as opposed to indirectly modulating the gut microbiota using faeces from healthy donors may be a safer and more durable therapy. Faecal microbiota transplantation (FMT) has been licensed by NICE since 2014 for the treatment of recurrent *Clostridium difficile* infection.^10^ FMT has shown promising results in clinical trials of several disease states resulting from gut dysbiosis beyond *C. difficile* infection,^10^ for example, in ulcerative colitis.^11–14^

We hypothesise that in patients with advanced cirrhosis, FMT may reduce the progression of chronic liver failure including the development of jaundice, ascites, bleeding, encephalopathy, infection and organ dysfunction. Whether FMT is feasible in the setting of cirrhosis remains to be investigated. We propose conducting a feasibility trial to determine whether FMT from a healthy donor will alleviate gut dysbiosis and immune dysfunction in advanced cirrhosis.

## Methods and analysis

### Primary objectives

The primary objective of this study will be to assess whether stabilising gut dysbiosis with FMT in patients with advanced cirrhosis is both feasible and safe.

### Primary endpoints

The primary endpoints of the study will be twofold. To assess the feasibility of FMT as determined by the recruitment rates (including the acceptability of the intervention) and tolerability of FMT, for example, gastro-oesophageal reflux rates. The second primary outcome measure will be to assess the safety of FMT administration, including the incidence of any transmissible bacterial or viral infection that is deemed to have been acquired from the donor including *C. difficile* infection.

### Secondary objectives

The secondary objectives of the study are to provide preliminary evidence of efficacy for a larger randomised trial, with the purpose of choosing the optimal primary outcome and estimating the parameters for sample size calculation. We will also collect blood, saliva, stool and urine samples from participants to assess the stability of the transplanted gut microbiome by comparing the percentage composition of the stool microbiota on day 7, 30 and 90 with the donor microbiome. Plasma endotoxin (and endotoxin binding protein), proinflammatory and anti-inflammatory cytokine levels, bacterial DNA quantification and serum procalcitonin will be performed at 7, 30 and 90 days as will changes in faecal biomarkers (calprotectin, lactoferrin and M2-pyruvate kinase).

### Trial design

A PROspective, randomised placebo controlled feasibility trial of Faecal mIcrobiota Transplantation (PROFIT) is a single-centre study. Thirty-two patients will be recruited from outpatient clinics at King’s College Hospital or from suitable inpatients on the wards. The patients will be recruited as per the inclusion and exclusion criteria listed in box 1. Patients will be randomised in a single-blinded fashion in a ratio of 3:1 FMT to placebo. Patients will be unaware of the intervention given, but investigators will not be blinded to the treatment intervention.Box 1Inclusion and exclusion criteriaInclusion criteria18–75 years.Confirmed advanced cirrhosis of any aetiology with a Model for End-Stage Liver Disease^15^ score between 10 and 16. The diagnosis of cirrhosis will be based on clinical, radiological or histological criteria.Patients with alcohol-related liver disease must have been abstinent from alcohol for a minimum of 6 weeks.Patients must be deemed to have a capacity to consent to the study.Exclusion criteriaSevere or life-threatening food allergy.Pregnancy or breast feeding.Patients treated for active variceal bleeding, infection, bacterial peritonitis, overt hepatic encephalopathy or acute-on-chronic liver failure within the past 14 days.Patients who have received antibiotics in the past 14 days.Active alcohol consumption of >20 g/day.Has had a previous liver transplant.Hepatocellular carcinoma outside of the Milan criteria.^20^
Inflammatory bowel disease.Coeliac disease.A history of prior gastrointestinal resection such as gastric bypass.Patient is not expected to survive the duration of the study (90 days).Severe renal impairment (creatinine >150 µmol/L).HIV positive.Immunosuppression, for example, more than 2 weeks treatment with corticosteroids within 8 weeks of intervention, active treatment with tacrolimus, mycophenolate, azathioprine.

### Patient and public involvement

A lay reviewer/patient representative at the National Institute for Health Research reviewed the protocol. This was funded by the Research for Patient Benefit programme. Feedback was taken on board and revisions were subsequently made.

The British Liver Trust, British Society of Gastroenterology Liver Research Group and King’s Liver Outpatient Advisory Group (patient group) were all involved in the study set-up and protocol development at all stages.

Results will be disseminated to study participants via the Liver Research Nurse if they indicate an interest in the study outcome.

### Patient population

The study will include all patients aged 18–75 years with a capacity to consent and a diagnosis of cirrhosis. Patients will have an MELD^15^ score of between 10 and 16. The diagnosis of cirrhosis may be based on radiological, clinical or histological parameters. In the case of alcohol-related cirrhosis, patients must have been abstinent for a minimum of 6 weeks. The exclusion criteria are outlined in box 2. Anticipated recruitment is outlined in figure 1.^16^

**Figure 1 F1:**
[figure not shown]
Study flow chart and anticipated recruitment. FMT, faecal microbiota transplantation.

### Consent

All participants will be asked to provide informed consent after having had the opportunity to discuss the trial with the clinician, their family and friends and having read the patient information sheet (PIS- see online supplementary file). Patients who lack capacity will not be enrolled in this study. If patients lose capacity during the trial follow-up period, an appropriate legal representative will be consulted and will provide consent to ongoing trial participation after appropriate discussion with the trials team and having read the PIS. If the legal representative does not agree to ongoing trial participation, the subject will be withdrawn from trial follow-up.

10.1136/bmjopen-2018-023518.supp1Supplementary data

### Study intervention

FMT is prepared in a laboratory at St Thomas’ Hospital in accordance with the principles of good manufacturing practice and under Manufacturing Authorisation for an Investigational Medicinal Product from the Medicines and Healthcare Products Regulatory Agency. FMT donors are healthy volunteers with no medical problems and normal body mass index. They must not be taking any regular medications and are rigorously screened for bloodborne and enteric pathogens prior to donation. Donors undergo questionnaire screening for risk factors at baseline and again at donation to reduce the risk of transmissible infection as outlined in box 2 (full questionnaire in online supplementary materials). Stool is processed (diluted and filtered with the addition of glycerol) within 6 hours of donation and stored at −80 °C for up to 6 months (as previously described).^17^ Material for FMT has full traceability from donor to recipient and aliquots of donor stool are kept for 30 years to allow further testing in the case of any adverse events. Placebo is a solution of saline with glycerol without faecal matter.Box 2Blood and stool testing of donor faecal microbiota transplantation samplesBlood (serology)HIV 1+2 serology.(human T-lymphotrophic virus) HTLV I/II Ab.Hepatitis A IgG (and if positive IgM).Hepatitis B surface antigen and core antibody.Hepatitis C virus antibody.Hepatitis E.Syphilis.cytomegalovirus (CMV)/Epstein Barr Virus (EBV) IgG/M.
*Strongyloides stercoralis* (ELISA).StoolPCR for gastroenteritis agents (*Campylobacter, Salmonella, Shigella* and *Escherichia coli* O:157).Ova, cysts and parasites x3.
*Clostridium difficile* test.Norovirus PCR.Screen for gentamicin and carbapenem-resistant Gram-negative organisms.Screen for methicillin resistant staphylococcus aureus (MRSA).Helicobacter pylori antigen.Entamoeba histolytica PCR.

10.1136/bmjopen-2018-023518.supp2Supplementary data

Following identification, all patients will attend a screening visit and sign the informed consent form. If deemed to be eligible, they will attend for a baseline visit with full clinical history and examination. Medication history will be recorded. Patients will complete a dietary questionnaire. Baseline samples of blood, urine, saliva and stool will be obtained. All patients will subsequently attend for a gastroscopy at which the FMT or placebo will be administered under direct visualisation into the jejunum via a nasojejunal tube. This will be performed as per the local Endoscopy Unit Protocol using topical local anaesthetic spray or midazolam sedation as per patient preference. Patients will first be asked to take bowel preparation to purge the bowel of its native bacteria. This consists of two sachets of Moviprep taken prior to gastroscopy. Patients will be monitored for side effects in the Clinical Research Facility after the procedure.

### Evaluations during and after treatment

Participants will be reassessed at 7 (±5), 30 (±7) and 90 (±7) days post-intervention. They will be reviewed in the Clinical Research Facility and undergo a physical examination, review of medications and dietary changes and adverse event monitoring. Samples of blood, urine, saliva and stool will be taken at these visits also. At the end of the 90-day follow-up period, patients will return to their usual care pathway.

### Statistical analysis

#### Sample size

This feasibility study will evaluate feasibility parameters using 95% CIs. The sample size has been proposed mainly to enable the trial to be conducted within the allocated budget and with acceptable precision for continuous outcomes. According to the simulation work by Teare *et al*,^18^ even with the relatively small pilot sample size of 20, the planned studies would have at least 80% power to detect the target effect size (for continuous outcomes) more than 75% of the time. Teare *et al* recommend that 60–100 subjects are sufficient to estimate an event rate (such as recruitment rates) with acceptable precision in a feasibility study, while sample sizes between 24 and 50 have been recommended for the accurate estimation of SDs. Therefore, we have chosen a sample size of 32 patients in this trial to have reliable data on all critical parameters (including event rates) which can also be used when planning a larger intervention trial. For event rates (eg, recruitment rates) and particularly in the extreme case with lower rates, for example, 10%, we estimate a drop of precision by only 5% using our updated sample size and the minimum recommended by Teare *et al* (0.16 for 60 patients vs 0.21 for 32 patients). Figure 2 illustrates the reduction in precision of different rates when the sample size increases for binary outcomes. This sample size will also be feasible within the budget and will provide acceptable information for planning a future large clinical trial.

**Figure 2 F2:**
[figure not shown]
CI width around one proportion (P) by sample size (N) from PASS software V.15.

The sample size of 32 patients will undergo randomisation in a 3:1 ratio. This will allow the study to demonstrate the feasibility of randomising, yet providing robust evidence with respect to the feasibility of the treatment and preliminary evidence of efficacy parameters.

The following feasibility criteria have been established:Twenty-five per cent of screened patients will consent: 256 patients will allow the estimate of the two-sided 95% CI of the proportion of consented patients, where the distance from the observed proportion to the limit is 0.058 units.Fifty per cent of patients screened will fulfil inclusion/exclusion criteria for the trial: screening 64 patients will allow the estimate of the two-sided 95% CI of the proportion of patients eligible, where the distance from the observed proportion to the limit is 0.128 units.Eighty per cent of randomised patients will complete treatment and follow-up: 26 of 32 patients completing will allow the estimate of the two-sided 95% CI for a single proportion, where the distance from the observed proportion to the limit is 0.177 units.

Differences between the placebo and treatment group in efficacy binary outcomes will be estimated along with the two-sided 95% CI (table 1). Assuming the proportion with the outcome in the control group is 0.5, our sample size will allow estimation of the half-width of the CIs for different size of differences as indicated below. Differences of 0.4 or higher will be distinguishable from 0.

**Table 1 T1:** Half-width of CIs for differences in proportions between two groups with given sample size, placebo group, p=0.5 (created with PASS software REF—PASS V.15)

Difference	0.1	0.2	0.3	0.4	0.5
Width	0.398	0.392	0.382	0.337	0.347

The half-width of the 95% CI of the difference in means for continuous outcome will be 0.889 SD.

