The study is not powered to detect differences in clinical outcomes, but may provide evidence for markers relating to clinical outcomes that could be studied in a larger randomised controlled trial.

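### The efficacy precision and the claim about differences of 0.4 assume all 32 patients are analysed, although the same section targets 26 completers; at 26 a difference of 0.4 is borderline, and even at 32 the claim holds only for an observed difference

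*Protocol article*

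**What the plan says.** All of this is in the Sample size part of the protocol article's Statistical analysis section, unless another place is named.

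- Size and allocation: "The sample size of 32 patients will undergo randomisation in a 3:1 ratio". The abstract gives the arms as 24 FMT and 8 placebo.
- Binary efficacy outcomes: "Differences between the placebo and treatment group in efficacy binary outcomes will be estimated along with the two-sided 95% CI". The planning assumption is "Assuming the proportion with the outcome in the control group is 0.5". Table 1 lists half-widths of 0.398, 0.392, 0.382, 0.337 and 0.347 for differences of 0.1, 0.2, 0.3, 0.4 and 0.5.
- The conclusion drawn from the table: "Differences of 0.4 or higher will be distinguishable from 0".
- Continuous outcomes: "The half-width of the 95% CI of the difference in means for continuous outcome will be 0.889 SD".
- Retention, as the third feasibility criterion: "Eighty per cent of randomised patients will complete treatment and follow-up: 26 of 32 patients completing".
- Discussion: "The study is not powered to detect differences in clinical outcomes".

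The section on data synthesis says that feasibility and efficacy outcomes will both be given 95% CIs, and that these serve success and go/no-go decisions.

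**The concern.** The efficacy precision is stated for full retention, while the same section would count 26 of 32 completing as meeting its target. A trial that just meets that target could therefore miss its stated precision for any outcome that needs the day-90 visit.

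Separately, the sentence about 0.4 has no probability attached and does not say whether the difference is observed or true. If the half-width is only a little smaller than the difference, an interval centred on a true 0.4 will often include 0 through sampling variation alone.

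The stake is interpretation. Efficacy results are meant to inform the design of a larger trial and go/no-go decisions. A reader who relies on the sentence could take an interval that includes 0 as evidence against an effect of 0.4, when such an interval is quite likely even if the effect is real.

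**Working it through.** **Inputs from the article.** 24 FMT and 8 placebo; two-sided 95% CI; placebo proportion 0.5; 26 of 32 completing.

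**Assumptions of this check.** The article does not say how 26 completers divide between arms, so 19/7 and 20/6 are both shown, with the exact 3:1 split (19.5/6.5) for reference. Non-completers are taken to have no day-90 data.

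**1. Reproducing the half-width for means.** Welch interval, in SD units: t(0.975, df) × √(1/n_FMT + 1/n_placebo).

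- 24/8: √(1/24 + 1/8) = 0.4082; df = 12.04; t = 2.178; product **0.889**, as stated.
- For comparison at 24/8, a normal quantile gives 0.800 and a pooled t gives 0.834.

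**2. Reproducing Table 1.** Wald half-width: 1.96 × √(0.25/n_placebo + p(1−p)/n_FMT), with p = 0.5 + difference.

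| Difference | Printed | Computed at 24/8 |
|---|---|---|
| 0.1 | 0.398 | 0.3981 |
| 0.2 | 0.392 | 0.3920 |
| 0.3 | 0.382 | 0.3816 |
| 0.4 | 0.337 | **0.3667** |
| 0.5 | 0.347 | 0.3465 |

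Four entries agree to within rounding. The 0.4 entry does not: 1.96 × √(0.25/8 + 0.09/24) = 1.96 × √0.035 = 0.367. The printed value is also smaller than the one for 0.5, although under this formula the half-width falls steadily as the difference grows. A continuity correction, the Newcombe interval and an equal 16/16 split do not give 0.337 while keeping the other entries. The 0.4 threshold still follows from the corrected value, since 0.367 < 0.4 while 0.382 > 0.3, but the margin is 0.033 and not the 0.063 that the printed entry implies.

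**3. The same formulas with 26 analysed.**

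| Analysed (FMT/placebo) | Half-width for means (SD) | Half-width at a difference of 0.4 |
|---|---|---|
| 24/8 | 0.889 | 0.367 |
| 19/7 | 0.976 | 0.394 |
| 19.5/6.5 | 1.017 | 0.407 |
| 20/6 | 1.068 | 0.421 |

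At 19/7 the half-width stays just under 0.4. At 20/6 and at exact 3:1 it exceeds 0.4.

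**4. Chance that the interval excludes 0 when the true proportions are 0.5 and 0.9.** Each figure is an exact sum over all pairs of binomial outcomes, except where a normal approximation is named.

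| Analysed | Wald | Fisher | Newcombe | Pooled z |
|---|---|---|---|---|
| 24/8 | 59% | 62% | 65% | 70% |
| 19/7 | 51% | 53% | 60% | 60% |
| 20/6 | 46% | 46% | 57% | 57% |

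At 24/8 the normal approximation gives 57% for Wald and 67% for pooled z. Wald is the method that reproduces Table 1. At a true difference of 0.5 the Wald chance at 24/8 is about 81% (normal approximation) to 86% (exact).

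**5. Observed differences.**

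- 24/8: 4/8 against 22/24 is a difference of 0.417 with a Wald lower limit of 0.05, so 0 is excluded.
- 20/6: 3/6 against 18/20 is a difference of 0.40 with a Wald lower limit of −0.02, so 0 is included. The Newcombe lower limit for the same data is +0.03.

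**The case against.** The strongest reply has four parts.

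*The retention figure is a benchmark, not planned attrition.* The 26 of 32 is a feasibility criterion, and nothing restricts the efficacy analysis to completers. Patients are also seen at days 7 and 30, so someone who misses day 90 may still contribute data. Analysis sets and missing data commonly belong to the SAP. This stands as a limit: the figures for 26 apply only to outcomes needing day-90 data, under the assumption stated. It does not remove the point that the precision is shown only for no loss.

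*The result at 26 depends on the split.* This also stands. A reader might infer that 0.4 is always lost at 26 analysed. It is not: 19/7 keeps the half-width below 0.4.

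*The sentence is about precision, not power.* Read as an observed difference of 0.4 with placebo at 0.5, it is correct at 24/8. That is a fair reading of a paragraph about half-widths. But the sentence does not say observed, and the table is set up from an assumed control proportion and given differences, so a reading as true differences is equally open. On that reading it overstates.

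*The article disclaims power.* A reader might infer that the sentence contradicts the Discussion's statement that "The study is not powered to detect differences in clinical outcomes". It does not strictly do so, because a precision statement can stand beside a disclaimer of power. The disclaimer softens the consequence, but does not correct the figures.

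**Conclusion.** The point holds in a limited form. The stated efficacy precision is a best case with all 32 analysed, although the section's own retention target is 26. Under the day-90 assumption and a 19/7 to 20/6 split, the half-width for means widens by about 10% to 20% (0.976/0.889 = 1.10; 1.068/0.889 = 1.20), and a difference of 0.4 lies at the edge of what the interval can separate from 0.

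With all 32, the sentence is right for an observed difference of 0.4 with placebo at 0.5. For a true difference of exactly 0.4 it describes an event with a chance of about 59% by the table's own method and no more than about 70% by any method tried. With 26 the chance is about 46-51% (Wald), or 46-60% across methods. These figures belong to a true difference of exactly 0.4 and should not be carried over to larger ones, where the chance is higher.

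The 0.4 entry in Table 1 is an error on its own inputs, whichever reading is taken.

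The primary endpoints, the sample size and the design are unaffected. The point is worth correcting because these intervals are meant to inform go/no-go decisions and the planning of a larger trial.

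**What to change.** 1. Correct the Table 1 half-width for a difference of 0.4 from 0.337 to 0.367, or state the method that yields 0.337.
2. Give Table 1 and the SD half-width for both 32 and 26 analysed, and show the split assumed for 26 (for example 19/7 and 20/6).
3. Replace the sentence about 0.4 with wording such as: *With all 32 analysed, an observed difference of 0.4 would have a 95% CI just excluding 0; a true difference of 0.4 would do so in roughly 60% of trials, and in about half with 26 analysed (Wald interval).*

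The cost is a change of wording and a recomputed table, with no extra patients. The downside is that the stated precision looks less favourable.

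### Table 1 prints a half-width of 0.337 for a difference of 0.4; the formula that fits its other columns gives 0.367, so precision there is overstated, although the 0.4 claim still holds

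*Protocol article*

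**What the plan says.** The Statistical analysis section of the protocol article, under Sample size, sets out the precision expected for binary efficacy outcomes:

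- Analysis: "Differences between the placebo and treatment group in efficacy binary outcomes will be estimated along with the two-sided 95% CI".
- Planning assumption: "Assuming the proportion with the outcome in the control group is 0.5".
- Arm sizes: "The sample size of 32 patients will undergo randomisation in a 3:1 ratio". The Abstract gives the split: "Twenty-four patients will be randomised to FMT plus standard of care" and "eight patients to placebo in a ratio of 3:1".
- Conclusion, placed just before the table: "Differences of 0.4 or higher will be distinguishable from 0".

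Table 1 is captioned "Half-width of CIs for differences in proportions between two groups with given sample size, placebo group, p=0.5". Its single row, labelled Width, reads 0.398, 0.392, 0.382, 0.337 and 0.347 for differences of 0.1, 0.2, 0.3, 0.4 and 0.5. The software is given as PASS V.15. No interval formula is named.

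**The concern.** The printed row falls from 0.398 to 0.337 and then rises to 0.347. With the placebo proportion fixed at 0.5, a larger difference moves the FMT proportion towards 0 or 1. Its variance then shrinks, so a simple half-width should keep falling across the row. The break is at 0.4, which is also the smallest difference that the text says can be told apart from zero. If that cell is wrong, a reader planning the larger trial from this table sees more precision at the stated threshold than 24 against 8 patients can give. A large enough error could also overturn the conclusion about 0.4, so its size has to be checked.

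**Working it through.** **Inputs, all from the protocol article**

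- FMT arm 24, placebo arm 8 (Abstract; the 3:1 split of 32 is repeated under Sample size).
- Placebo proportion 0.5, two-sided 95% interval, so z = 1.96 (Sample size).
- FMT proportion p = 0.5 + difference. Taking 0.5 - difference gives the same result, because p(1-p) is symmetric about 0.5.

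**Formula (unpooled Wald)**

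half-width = 1.96*sqrt(0.5*0.5/8 + p(1-p)/24)

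**Reproducing the row**

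| Difference | p | Variance sum | Half-width | Printed |
|---|---|---|---|---|
| 0.1 | 0.6 | 0.03125 + 0.01000 = 0.04125 | 0.398 | 0.398 |
| 0.2 | 0.7 | 0.03125 + 0.00875 = 0.04000 | 0.392 | 0.392 |
| 0.3 | 0.8 | 0.03125 + 0.00667 = 0.03792 | 0.382 | 0.382 |
| 0.4 | 0.9 | 0.03125 + 0.00375 = 0.03500 | **0.367** | **0.337** |
| 0.5 | 1.0 | 0.03125 + 0 = 0.03125 | 0.3465 | 0.347 |

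Three cells match exactly. The 0.5 cell is within 0.001: the unrounded value is 0.34648, and entering p as 0.999 instead of 1 gives 0.3467, which rounds to the printed 0.347. Only the 0.4 cell fails.

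**Floor set by the placebo arm**

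The placebo term alone gives 1.96*sqrt(0.25/8) = 0.346, and the FMT term can only add to it. A half-width of 0.337 needs a variance sum of (0.337/1.96)^2 = 0.0296, which is less than the placebo term of 0.03125. No FMT proportion can produce that, and rounding cannot explain it.

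**Other interval methods**

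The variants tried were:

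- continuity-corrected Wald, a t critical value and pooled variance;
- Newcombe with and without continuity correction, Farrington-Manning and Agresti-Caffo;
- swapped arm sizes, 16 against 16, and about 20% dropout.

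None reproduces the row. Two come close at 0.4 only:

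| Method | 0.1 | 0.2 | 0.3 | 0.4 | 0.5 |
|---|---|---|---|---|---|
| Printed | 0.398 | 0.392 | 0.382 | 0.337 | 0.347 |
| Agresti-Caffo | 0.363 | 0.358 | 0.349 | 0.336 | 0.319 |
| Newcombe, distance to lower limit | 0.346 | 0.348 | 0.346 | 0.337 | 0.316 |

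Both miss the other four columns clearly.

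**Effect at a difference of 0.4**

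- Printed half-width: 0.4 - 0.337 = 0.063 and 0.4 + 0.337 = 0.737.
- Recomputed half-width: 0.4 - 0.367 = 0.033 and 0.4 + 0.367 = 0.767.
- Ratio of half-widths: 0.367/0.337 = 1.09.
- Ratio of margins above zero: 0.033/0.063 = 0.52.

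**Does the threshold statement survive?**

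- At 0.3 the half-width of 0.382 exceeds the difference, so the interval includes zero.
- At 0.4 the half-width of 0.367 is smaller than the difference, so the interval excludes zero.
- At 0.5 the half-width of 0.346 is smaller again.

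So 0.4 remains the first tabulated difference that excludes zero. Solving d = 1.96*sqrt(0.25/8 + (0.25 - d^2)/24) puts the exact crossing at about d = 0.37.

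**The case against.** The strongest reply is that nothing depends on this cell. The article bases the 32 patients on budget and on precision for continuous outcomes. It says the trial is not powered for clinical outcomes, and its listed feasibility criteria use single-proportion intervals rather than Table 1. The binary efficacy comparison serves the secondary objectives. All of this stands, and it makes the point a small one.

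A second reply is that the article names only the software, so the Wald method is an inference, and the impossibility argument holds only under that method. This also stands. The inference is nevertheless strong: three exact matches, one within 0.001, and no tested alternative that fits the whole row. A single row should come from a single method.

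A reader might go further and infer that the error defeats the article's statement about differences of 0.4 or more. The document does not support that. The statement needs a half-width below 0.4, and 0.367 meets it. The sentence quotes no lower limit, so it contains no wrong figure; the limits 0.063 and 0.033 are derived here from the table.

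**Conclusion.** The 0.4 cell of Table 1 is wrong as printed: 0.337 should be 0.367. The two values differ in one digit, so a transcription slip is the likely cause, though the document cannot confirm that. The printed cell is about 8% too small (0.337/0.367 = 0.92). The margin above zero at the article's own threshold is about half of what the table implies. The conclusion about 0.4 remains true, and sample size, endpoints and design do not change.

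This rests on arms of 24 and 8 with no dropout, a placebo proportion of exactly 0.5, and the Wald interval inferred from the other columns. It is a minor correction to a stated precision figure.

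**What to change.** Change the 0.4 entry of Table 1 from 0.337 to 0.367, and label the row as half-width so that it agrees with the caption; a reader who takes the present label literally would halve the values. The sentence about differences of 0.4 or higher can stay as it is. Naming the interval method beside the software reference would be a useful addition, since the formula now has to be inferred.

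The cost is one cell and one row label. The printed precision at 0.4 becomes slightly less favourable, and no analysis or sample size has to be reworked.
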